However, there are no data at present to support the efficacy of CP treatment in MERS-CoV infection; therefore, it has been recommended to administer CP only in the context of a clinical trial. While an RCT will be required to evaluate effectiveness, evaluating effectiveness on clinical endpoints such as mortality will likely require several hundred to several thousand seriously ill MERS-CoV patients in order to achieve sufficient statistical power, anticipating reasonable potential effect sizes. Additionally, CP from different MERS-CoV survivors will likely contain differing levels of neutralizing anti-MERS-CoV antibodies. Since seriously ill MERS-CoV-infected patients may have detectable viral RNA in various locations that can be sampled (for example lower respiratory tract secretions) for prolonged periods, it might be possible to first determine the relationship between neutralizing antibody dose and antiviral effects on clinical and laboratory features in a small open-label study. This information would be very helpful to design of an RCT and in determining the most appropriate neutralizing antibody dose, or dosing range for the study. This may also inform dose selection for follow-on anti-MERS-CoV antibody preparations currently in pre-clinical development (for example, neutralizing human monoclonal antibodies, polyclonal human neutralizing immunoglobulin derived from transchromosomic cattle (personal communication, [name]).

Therefore, we plan to conduct a 2-phase study. In the first phase (CP collection phase), we will explore the feasibility of collection of CP from donors who have significant titers of anti-MERS-CoV antibodies. In the second phase, patients with MERS-CoV infection will be treated with CP. If the protocol is feasible, safe, and associated with temporal changes in viral load and illness, this pilot study will inform a larger concealed intervention, placebo-controlled RCT that is powered to evaluate efficacy of CP on relevant clinical outcomes.

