#### CP therapy phase

We will screen consecutive critically ill patients admitted to the intensive care unit or other areas of the hospital where critically ill patients receive care for the following criteria:

Inclusion criteriaCritical illness as defined by one or more of the following: admission to an ICU; current receipt of mechanical invasive or non-invasive ventilation; partial pressure of oxygen to fraction of inspired oxygen ratio (PaO2:FiO2) of <300 mmHg; current receipt of intravenous vasoactive medications to maintain mean arterial pressure >65 mmHg; new-onset (since development of MERS-CoV symptoms) receipt of renal replacement therapy or extra-corporeal life support.Laboratory-confirmed MERS-CoV infection (by real-time reverse-transcription polymerase chain reaction rRT-PCR).Age of more than or equal to 14 years.

Exclusion criteriaSymptomatic illness exceeding two weeks (14 days) at time of enrollment.Negative rRT-PCR from respiratory secretions or blood within 48 h prior to assessment of eligibility.History of allergic reaction to blood or plasma products (as judged by the investigator).Known IgA deficiency.Medical conditions in which receipt of 500 mL intravascular volume may be detrimental to the patient (e.g., actively decompensated congestive heart failure).

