#### Frequency and duration of follow-up

Clinical and laboratory data will be collected at baseline, 30 min after first dose, 30 min after second dose, study days 1, 3, 5, 7, 14, and 28.

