#### CP therapy phase

We will establish safety of the study intervention, as measured by number of serious adverse events related to study intervention (adverse events include development of complications of intravascular volume overload and clinical pulmonary edema by temporally related-shortness of breath, chest radiograph findings and change in oxygenation requirements; development of transfusion-related acute lung injury (TRALI) or substantial allergy or anaphylaxis). These serious events will be adjudicated by a committee of 3 investigators.*Clinical Outcomes* We will measure (1) sequential organ failure assessment (SOFA) scores on study days 1, 3, 5, 7, 14, and 28 (2) requirement for organ support (oxygen and ventilation; dialysis; vasopressors) after enrollment; (3) length of stay in ICU defined as the number of calendar days between admission and final discharge from ICU for the same ICU admission of enrollment; and duration of mechanical ventilation, defined as the number of calendar days between start and final liberation from mechanical ventilation for the same ICU admission of enrollment and hospital length of stay as defined as the number of calendar days between admission to hospital and final discharge from hospital for the same hospital admission; and (4) vital outcome (mortality) in ICU, hospital and at 28 days.Other clinical outcomes include “ICU-free days”, defined as the number of days that patients are not in ICU in the first 28 days after enrollment. Patients who die within 28 days will be counted separately, and not categorised by ICU-free days. Similarly, “ventilator-free days” is defined as the number of days that patients do not receive mechanical ventilation in the first 28 days after enrollment. “Renal replacement therapy-free days” and “vasopressor-free days” are defined in a similar way. Serial chest radiograph findings, as obtained by the clinical team will also be recording as per case report form, graded as unilateral or bilateral infiltrates, in 1–4 quadrants.*Laboratory Outcomes* We will measure the following laboratory outcomes:The serum level of anti-MERS-CoV antibodies before and after administration of CP.MERS-CoV viral load (the primary laboratory outcome is viral clearance from all sampled sites by day 3 after administration of CP).

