### Statistical analyses

#### Analysis of viral load data

Serial MERS-CoV viral load measurements will be displayed as box and whisker plots for the 20 treated patients against time.The probability of a patient having an undetectable viral load from all sampled sites by day 3 after administration of therapy will be estimated by the proportion of the 20 treated patients for whom this occurs. An exact, conservative, two-sided confidence interval for this probability will be calculated using the method of Clopper and Pearson (1934).The relationship between log viral load at day 3 and the neutralizing antibody dose received will be characterised by fitting a regression model to the data from the 20 treated patients. The log viral load at baseline will be included in this model.The relationship between the probability of a patient having an undetectable viral load by day 3 and the neutralizing antibody dose received will be characterised by fitting a log-logistic regression model to the data from the 20 treated patients. The log viral load at baseline will be included in this model.

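### Primary laboratory outcome: the all-sampled-sites rule is easier to meet with fewer samples and can count patients undetectable before infusion as cleared, so the reported proportion can be inflated

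*Protocol article*

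**What the plan says.** Under Outcome measures, CP therapy phase, the Protocol article says that "the primary laboratory outcome is viral clearance from all sampled sites by day 3 after administration of CP". Under Analysis of viral load data, the estimated quantity is "The probability of a patient having an undetectable viral load from all sampled sites by day 3 after administration of therapy", which "will be estimated by the proportion of the 20 treated patients for whom this occurs". The precision statement follows: "An exact, conservative, two-sided confidence interval for this probability will be calculated using the method of Clopper and Pearson (1934").

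Three other places bear on who is positive at the start and what is sampled:

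- **Entry.** Patients need "Laboratory-confirmed MERS-CoV infection (by real-time reverse-transcription polymerase chain reaction rRT-PCR"), with no time window and no site given. One exclusion is "Negative rRT-PCR from respiratory secretions or blood within 48 h prior to assessment of eligibility".
- **Schedule.** Frequency and duration of follow-up gives times but no sites: "Clinical and laboratory data will be collected at baseline, 30 min after first dose, 30 min after second dose, study days 1, 3, 5, 7," and then days 14 and 28.
- **Sites.** The Background notes that "seriously ill MERS-CoV-infected patients may have detectable viral RNA in various locations that can be sampled", with lower respiratory secretions as an example. The sample size section mentions respiratory tract and blood. No section of the article says which sites must be sampled in a treated patient.

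Baseline log viral load is a covariate in the day-3 regression models. It plays no part in the proportion itself.

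**The concern.** The rule that decides success depends on two things other than what happens to the virus after plasma.

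The first is sampling. A patient succeeds if every sample that happens to be taken is negative. With only blood taken, one negative is enough; with blood and a respiratory sample, both must be negative. If a respiratory site was positive at baseline and is not sampled at day 3, its positivity drops out of the judgement. Sampling may well vary, because the critical-illness criterion can be met by ICU admission or by PaO2:FiO2 below 300 mmHg alone, so not every patient need be intubated.

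The second is baseline status. The denominator is all 20 treated patients, and nothing requires a positive sample immediately before infusion. A patient who is undetectable at that point and stays so is a success to which plasma contributed nothing.

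The study is single-arm, so no control group shares these artefacts and cancels them. The Background makes temporal change in viral load one of the conditions for going on to a larger trial, and the Conclusions expect the data to show how antibody titre relates to viral clearance. A clearance figure that moves with sampling intensity is a weak basis for either. The Clopper-Pearson interval covers chance variation only, not differences in what was sampled.

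**Working it through.** **The plan's own figure.** The only stated sample-size result concerns survival, not clearance: 17 or more of 20 alive against 60%. The doubled exact tail is 2 × P(X ≥ 17 | n = 20, p = 0.60) = 2 × 0.01596 = 0.0319, which agrees with the stated 0.032. The article gives no expected clearance rate, so everything below is illustrative and every rate is an assumption.

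**Step 1: fewer sites make the rule easier.** For any patient, P(all k sites negative) cannot rise as k increases. If each site clears with probability 50% independently, success is 50% with one site, 0.5² = 25% with two and 0.5³ = 12.5% with three.

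**Step 2: a mixed cohort.** Let f be the share of patients judged on blood alone. Assume day-3 clearance of 70% in blood and 20% in the respiratory tract. With both sites sampled, success is 0.70 × 0.20 = 14% if the sites are independent. It is 20% if they are nested, meaning that everyone who clears the respiratory tract has also cleared blood. The reported proportion is (1 − f) × (14% or 20%) + f × 70%:

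| f | independent | nested |
|---|---|---|
| 0% | 14% | 20% |
| 10% | 20% | 25% |
| 25% | 28% | 33% |
| 50% | 42% | 45% |

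The biology is the same in every row; only the sampling changes.

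**Step 3: patients undetectable before infusion.** Let b be their number, assume they stay undetectable, and let q be the clearance rate among the other 20 − b. The plan reports (b + (20 − b)q)/20, which exceeds q by b(1 − q)/20. At q = 20% each such patient adds 0.80/20 = 4 percentage points: b = 0, 1, 2, 4 gives 20%, 24%, 28%, 36%.

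In counts, take b = 3 and 5 clearances among the other 17. The plan reports (3 + 5)/20 = 8/20 = 40%; among patients with virus to clear it is 5/17 = 29%. The gap is 3 × (12/17)/20 = 10.6 points.

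**Step 4: does the exclusion make b zero?** Set the entry criteria against the estimator:

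- A known negative in respiratory secretions or blood within 48 hours before eligibility assessment bars entry. This keeps b small.
- The exclusion acts only if a test was done in that window. Confirmation of infection has no time limit, so an older positive with no recent test satisfies both criteria.
- The window closes at eligibility assessment, not at infusion. A baseline sample is scheduled, but no section of the article makes its result a condition for treatment or for the denominator.

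So b is limited but not forced to zero, and the documents give no value for it.

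**Step 5: scale against chance.** Assuming a 95% level, which the article does not state, the Clopper-Pearson intervals are 19.1% to 63.9% for 8/20 and 10.3% to 56.0% for 5/17. They overlap for most of their length.

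**The case against.** The strongest reply has five parts.

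- **Net direction.** A reader might infer that the proportion is biased upward as a matter of fact. The documents do not show this. Patients who die or have no sample by day 3 stay in the denominator of 20, and if they count as not cleared they pull the estimate down; the article does not say how they count. For a patient sampled at several sites, the all-sites rule is also at least as strict as any single-site rule. This stands: the proportion can be inflated, but a net upward bias is not established.
- **Baseline negatives.** A reader might infer that the plan freely admits PCR-negative patients. It does not; the 48-hour exclusion bars known recent negatives at either site. This stands in part: it narrows the problem but does not close it.
- **The words about day 3.** Read literally, a negative on day 1 followed by a positive on day 3 could count as clearance. Nothing in the article says it would, and this is one reading of ordinary wording. It is a reason to tidy the definition, not a fault in itself.
- **Use of the figure.** A reader might infer that this proportion will set the clearance rate assumed for the later trial. No section says so. The Background and Discussion direct that trial at clinical outcomes and mortality, and assign the viral data mainly to the antibody-dose relationship, where the models adjust for baseline load. This stands, and it lowers the stakes.
- **Condensed article.** Specimen lists and missing-sample rules may sit in the full protocol or analysis plan, so their absence here is no finding. That does not answer the point, which concerns a rule the article does state: all sampled sites, over all 20.

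**Conclusion.** The point holds in a limited form. The stated primary laboratory outcome is easier to meet with fewer samples and gives credit to any patient undetectable before infusion, and nothing in the article prevents either. The 48-hour exclusion makes the second route narrow but leaves it open.

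The size cannot be derived from the documents. The contrast of 40% with 29% rests on assumed counts (3 undetectable at baseline, 5 of 17 clearing), and the sites table rests on assumed clearance of 70% in blood and 20% in the respiratory tract. At n = 20, shifts of this order lie well inside the confidence interval. What the correction gains is a clearly defined quantity rather than precision. It is worth making because this is the named primary laboratory outcome, there is no control arm, and the change is cheap.

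**What to change.** In the laboratory outcomes paragraph and in Analysis of viral load data:

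1. Define clearance as undetectable rRT-PCR in the day-3 sample at every site that was positive in the pre-infusion sample.
2. Use as denominator the treated patients detectable at one or more sites at baseline, and report how many of the 20 were not.
3. Count death before day 3, or no day-3 result at a baseline-positive site, as not cleared. Add a sensitivity analysis that leaves out patients whose day-3 sample is missing, because a patient who improves may no longer be able to give a respiratory sample.
4. Report results separately for respiratory tract and blood. A patient sampled only in blood from the start is still judged on blood alone under item 1, so the by-site figures are needed to show this.
5. Keep the all-sampled-sites proportion of 20, with its Clopper-Pearson interval, as a secondary description.

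**Cost.** The change is to wording, plus the discipline of re-sampling at day 3 every site that was positive at baseline. Baseline and day-3 collection times are already scheduled, though the article does not say at which sites. The denominator becomes slightly smaller, the interval wider and the rate possibly less favourable.

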### Laboratory procedures

**Measuring anti-MERS-CoV antibodies level in donor and participant serum**MERS-CoV antibodies will be tested first by the enzyme linked immunosorbent assay (ELISA) as a screening test (Drosten et al. 2014; Müller et al. 2015) according to manufacturer’s instructions (Euroimmun AG, Lübeck, Germany). Results will be reported as the optic density (OD) ratio, which is calculated as the OD value of the patient’s sample divided by the calibrator OD value. We will use the cut-off values recommended by the manufacturer: a ratio of <0.8 is considered negative, >0.8 and <1.1 borderline and a ratio of >1.1 is considered positive.Confirmation will be done by the Indirect Fluorescent Antibody (IFA, Euroimmun AG, Lübeck, Germany) according to manufacturer’s instructions. Samples with ≥1:10 will be considered reactive according to the manufacturer’s instructions, subjects will be considered candidate for plasma donation if they have titers of ≥1:160; which is a similar threshold to what has been used in a convalescent plasma trial for H1N1 influenza (Hung et al. 2011).

### Administrative and ethical aspects

The primary coordinating study center is the Intensive Care Department at King Saud bin Abdulaziz University for Health Sciences (KSAUHS) in Riyadh, Saudi Arabia. The study will be conducted in accordance with the ethical principles of the Declaration of Helsinki and the International Conference on Harmonization-Good Clinical Practice (ICH-GCP) guidelines.

Several measures will be taken to ensure optimal compliance with the study protocols. Before launching the study, ICU physicians and nurses will attend the training sessions with special emphasis on any adverse events noted during the intervention. The Steering Committee, led by the principal investigator, will be responsible for overseeing the conduct of the trial, for upholding or modifying study procedures as needed, addressing challenges with protocol implementation, formulating the analysis plan, reviewing and interpreting the data and preparing the manuscript. The study also has an independent data safety monitoring board (DSMB) which is responsible for reviewing reports submitted to the regarding safety of study patients, protocol adherence and may making recommendations to continue or terminate the study based on safety analysis results. The DSMB, composed of 5 members (who are named at the end of this document) will meet at the beginning of phase II of the study followed by 6-monthly or as needed.

#### Safety measures

In the event of an acute transfusion reaction, the transfusion will be stopped immediately and must be reported to the blood bank the principal investigator immediately as well as to the study management committee. All the serious adverse events (SAE) adjudicated as related to the study intervention will be reported to the Institutional Research Ethics Board and the DSMB.

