### Statistical and analytical plan

#### Sample size calculation

This is an exploratory study, aimed at rectifying the current lack of information on the use of CP to treat MERS-CoV infection. Due to the exploratory nature of this study and the paucity of sequential data on viral RNA levels in respiratory tract and blood samples from MERS-CoV-infected patients, and on their clinical progress, the sample size is fixed at 20, which is a realistic target for a study of 12 months duration. The sample size of 20 is sufficient to reach a conclusion that the 28-day survival rate significantly exceeds 60 % (p = 0.032, 2-sided) if 17 or more patients survive for the 28 days of follow-up. This would represent promising evidence to motivate a full-scale comparative clinical trial.

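### The only SAE route to the DSMB and ethics board that the article states is for events judged related, and a count of those events in 20 patients cannot establish safety

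*Protocol article*

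**What the plan says.** Under Outcome measures, CP therapy phase, the protocol article states its safety objective: "We will establish safety of the study intervention, as measured by number of serious adverse events related to study intervention". It names volume overload and pulmonary edema (recognised by dyspnoea, chest film and oxygen need), TRALI, and serious allergy. On judgement it says: "These serious events will be adjudicated by a committee of 3 investigators". Whether these three are independent of the trial team is not stated.

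Under Safety measures, the onward route is "All the serious adverse events (SAE) adjudicated as related to the study intervention will be reported to" the ethics board and the DSMB. Acute transfusion reactions have a separate, immediate route to the blood bank, the principal investigator and the study management committee. No route is given for SAEs judged unrelated.

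Under Administrative and ethical aspects, an independent five-member DSMB reviews safety and adherence reports, whose content is not described, and may recommend continuing or terminating. It "will meet at the beginning of phase II of the study followed by 6-monthly or as needed".

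On size: "the sample size is fixed at 20, which is a realistic target for a study of 12 months duration".

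**The concern.** A relatedness filter does little damage when the harm is distinctive. Here most of the named harms are respiratory, and the patients are enrolled because they are critically ill, often ventilated or with impaired oxygenation. New infiltrates or a rising oxygen requirement after plasma may be the plasma or the disease. The Background calls the study open-label. The Informed consent section allows untreated patients to be sampled observationally, but every stated model and proportion uses the 20 treated patients, so no planned comparison would show an excess of deterioration.

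The relatedness call therefore carries much of the weight, and a monitoring board adds value by being able to disagree with it. If only events already called related are forwarded, the board can question the positive calls but not the negative ones.

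The result also feeds a decision: the Background and the Discussion both make safety a condition for going on to the randomized trial.

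**Working it through.** **1. The plan's own figure.** The article gives no safety figure. Its one computed figure is the survival rule: success "if 17 or more patients survive for the 28 days of follow-up", tested against 60%, with "p = 0.032, 2-sided". The exact binomial tail is P(X ≥ 17 | n = 20, p = 0.6) = 0.01596, and doubled it is 0.0319. The figure reproduces. It does not bear on safety, but it confirms n = 20.

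**2. Who is stated to receive what.**

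| Event | Judged by | Stated recipients |
|---|---|---|
| SAE adjudicated related | three investigators | ethics board, DSMB |
| SAE adjudicated unrelated, including death | three investigators | none stated |
| Acute transfusion reaction | not filtered | blood bank, principal investigator, study management committee |
| Vital status, SOFA, organ support, radiographs | not filtered | recorded for all patients; supply to DSMB not stated |

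The unrelated row need not be small. The survival benchmark of 60% corresponds to 20 × 0.40 = 8 deaths. That is a benchmark, not a forecast.

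**3. What a count in 20 can show.** Take x as patients with at least one related SAE, with Clopper-Pearson limits at 95% (level assumed).

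- x = 0: upper limit 1 − 0.025^(1/20) = 16.8%. The one-sided 95% limit is 1 − 0.05^(1/20) = 13.9%.
- x = 1: 0.1% to 24.9%.
- x = 2: 1.2% to 31.7%.
- x = 3: 3.2% to 37.9%.
- A true rate of 5% gives no event with probability 0.95^20 = 36%.

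These figures describe 20 patients with perfect attribution. They test the claim to establish safety and do not measure the filter.

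**4. What the filter could do.** The article gives no harm or attribution rates, so these inputs are assumptions. Let e be the proportion of patients with a plasma-caused SAE and s the share of those called related. Let b be the proportion with a disease-caused SAE and f the share of those called related. With the two groups not overlapping, the expected related count is 20(es + bf).

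*Missed harm* (f = 0), where the chance of no related report is (1 − es)^20:

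| e | s | Expected count | Chance of zero |
|---|---|---|---|
| 20% | 1 | 4 | 1.2% |
| 20% | 0.5 | 2 | 12% |
| 20% | 0.25 | 1 | 36% |
| 10% | 1 | 2 | 12% |
| 10% | 0.5 | 1 | 36% |
| 10% | 0.25 | 0.5 | 60% |

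*Disease counted as harm* (e = 0), with b = 40% borrowed from the benchmark:

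- f = 0.125: expected count 20 × 0.40 × 0.125 = 1; chance of at least one report 1 − 0.95^20 = 64%.
- f = 0.25: expected count 20 × 0.40 × 0.25 = 2; chance of at least one report 1 − 0.90^20 = 88%.

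An expected related count of 2 thus arises when plasma harms one patient in five and half of those events are recognised. It also arises when plasma harms nobody and a quarter of disease events are blamed on it. The related count alone cannot separate the two.

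**The case against.** The strongest reply is that the article says what the DSMB will be sent, not what will be kept from it. The board has a broader remit over safety reports and safety analyses, and a charter or full protocol may provide for all-SAE listings. That stands: a reader might infer that unrelated events are withheld, and the text does not say so. What remains is that the one rule the article does state carries the filter.

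Other stronger readings also fail:

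- *That the adjudicators are the trial's own staff.* Independence is neither stated nor denied.
- *That harm would go unseen.* Death, SOFA, organ support and radiographs are recorded whatever the attribution, 28-day death gets an exact interval, and acute reactions are reported at once without adjudication.
- *That the related count is biased downward.* The working shows error in both directions, and the article's emphasis on timing after transfusion could draw disease events in.
- *That DSMB meetings are too sparse.* The text allows extra meetings when needed.

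It can also be said that the study is openly exploratory, that 20 patients is a stated practical limit, and that an interval for SAEs may be left to the analysis plan. These are fair. The missing interval is not an error in itself. But the article fixes the safety measure as a number of related events and claims that this number will establish safety, which no analysis of 20 patients can support.

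**Conclusion.** The concern holds in this limited form. The only SAE route to the DSMB and ethics board stated in the article depends on a relatedness judgement that is unreliable in this setting. On that route the board need not see the events it would need in order to challenge the judgement. Separately, a related count of 0 or 1 in 20 leaves true rates up to 16.8% or 24.9% open, so safety can be estimated but not established.

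The interval figures rest on n = 20, a 95% level and counting patients rather than events. The attribution figures rest on assumed rates and show only that the effect could be material. Nothing here shows that events are withheld or that the count errs in a known direction. The change is advisable rather than critical: the study is exploratory and all-cause outcomes are recorded, but its safety result is a condition for the randomized trial.

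**What to change.** - **Safety measures:** state that the DSMB receives all SAEs and all deaths regardless of attribution, with the adjudicated relation shown beside each. If a charter already provides this, say so here.
- **Outcome measures, CP therapy phase:** report the number of patients with at least one event of the listed types out of 20, with the Clopper-Pearson interval already planned for viral clearance and 28-day death. Give it twice: regardless of attribution, and for events adjudicated as related.
- **Same section:** replace *establish* with *estimate* in the safety objective.

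The cost is a few sentences, a short listing and slightly more reading for the DSMB. No extra patients, visits or assessors are needed.
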